# Optimization of Nutrition And Medication (OptiNAM) for acutely admitted older patients: protocol for a randomized single-blinded controlled trial

**DOI:** 10.1186/s13063-021-05456-6

**Published:** 2021-09-14

**Keywords:** Drug utilization Review, Potentially inappropriate medication list, Glomerular filtration rate, Pharmacogenetics, Malnutrition, Quality of life, Gastrointestinal microbiome, Frailty, Geriatrics, Emergency service, Hospital

## Abstract

**Background:**

Internationally, older patients (≥65 years) account for more than 40% of acute admissions. Older patients admitted to the emergency department (ED) are frequently malnourished and exposed to inappropriate medication prescribing, due in part to the inaccuracy of creatinine-based equations for estimated glomerular filtration rate (eGFR). The overall aims of this trial are to investigate: (1) the efficacy of a medication review (MED intervention) independent of nutritional status, (2) the accuracy of eGFR equations based on various biomarkers compared to measured GFR (mGFR) based on ^99m^Technetium–diethylenetriaminepentaacetic acid plasma clearance, and (3) the efficacy of an individualized multimodal and transitional nutritional intervention (MULTI-NUT-MED intervention) in older patients with or at risk of malnutrition in the ED.

**Methods:**

The trial is a single-center block randomized, controlled, observer-blinded, superiority and explorative trial with two parallel groups. The population consists of 200 older patients admitted to the ED: 70 patients without malnutrition or risk of malnutrition and 130 patients with or at risk of malnutrition defined as a Mini Nutritional Assessment-Short Form score ≤11. All patients without the risk of malnutrition receive the MED intervention, which consists of a medication review by a pharmacist and geriatrician in the ED. Patients with or at risk of malnutrition receive the MULTI-NUT-MED intervention, which consists of the MED intervention in addition to, dietary counseling and individualized interventions based on the results of screening tests for dysphagia, problems with activities of daily living, low muscle strength in the lower extremities, depression, and problems with oral health. Baseline data are collected upon study inclusion, and follow-up data are collected at 8 and 16 weeks after discharge. The primary outcomes are (1) change in medication appropriateness index (MAI) score from baseline to 8 weeks after discharge, (2) accuracy of different eGFR equations compared to mGFR, and (3) change in health-related quality of life (measured with EuroQol-5D-5L) from baseline to 16 weeks after discharge.

**Discussion:**

The trial will provide new information on strategies to optimize the treatment of malnutrition and inappropriate medication prescribing among older patients admitted to the ED.

**Trail registration:**

ClinicalTrials.gov NTC03741283. Retrospectively registered on 14 November 2018.

**Supplementary Information:**

The online version contains supplementary material available at 10.1186/s13063-021-05456-6.

## Introduction

### Background

Internationally, older patients (≥65 years) account for 41–46% of acute admissions [1–3]. Among older patients admitted to the emergency department, the prevalence of the risk of malnutrition and malnutrition ranges between 35 and 71% in acutely admitted older patients [4–8] and the prevalence of polypharmacy (≥5 prescribed medications) is 73–77%, while 51–85% receive at least one potentially inappropriate medication (PIM) [9–12]. Both malnutrition and polypharmacy are associated with decreased quality of life [13–16], and these risk factors are often comorbid, as 64–87% of older patients at risk of malnutrition present with polypharmacy [5, 6, 9]. However, interventions to address malnutrition and inappropriate medication prescribing in the ED are limited by the acute setting. The median length of stay (LOS) for acutely admitted older medical patients is 2.2–4.5 days [17, 18], and more than half of all patients admitted to the ED are discharged without being transferred to another department [6, 8, 19]. Consequently, some of these patients will be discharged before initiatives to overcome malnutrition or inappropriate medication have been started. Therefore, it is essential that interventions to optimize nutritional care and medication prescribing are started in the ED and continued after discharge (transitional care).

#### Inappropriate prescribing and medication review intervention

Polypharmacy is common among older patients in part because medications are readily prescribed for new conditions, but the appropriateness of continuing each medication is rarely evaluated [20–22]. Polypharmacy and other causes of inappropriate medication prescribing may lead to adverse drug reactions, which are responsible for up to 15% of unplanned hospitalizations [23]. Therefore, dose adjustment and deprescribing of inappropriate medications are important components of medication reviews for older patients [24]. Medication optimization in older patients is challenging due to the presence of comorbidities and individual variations in age-related physiological changes including pharmacokinetic, pharmacogenetic, and pharmacodynamic responses to medications [25, 26].

Pharmacist-led medication reviews have been proposed as an important component of optimizing medication prescribing [27], but there is conflicting evidence regarding the impact and efficacy of medication reviews for older patients in the ED [28–32]. International studies have shown that collaboration between pharmacists and physicians in multidisciplinary hospital teams can decrease inappropriate prescribing among older patients in a transitional setting [33–35]. We have previously shown that a medication review in the ED is feasible and led to increased medication appropriateness between admission and discharge in 64% of the patients [36]. However, this finding has never been demonstrated among older patients in the ED using a randomized controlled trial. Therefore, we aim to use a randomized controlled trial to determine the efficacy of a medication review (MED intervention) in a cohort of acutely admitted older patients both without and with risk of malnutrition.

#### Accuracy of estimated glomerular filtration rate in older medical patient

Another challenge during medication optimization is the accurate assessment of renal function [37, 38]. This is important because approximately 40% of all medications require dose adjustment according to renal function [39]. In clinical practice, renal function is typically determined with estimated glomerular filtration rate (eGFR) based on the measurement of serum creatinine. However, serum creatinine is heavily dependent on non-GFR determinants such as muscle mass, nutritional status, and sex, which can result in inaccurate eGFR and, therefore, inappropriate prescribing of renally cleared medications among older patients [40, 41]. Alternative markers of kidney function such as cystatin C, beta-trace protein (BTP), and beta-2-microglobulin (B2M) are less dependent on muscle mass, age, and sex compared to serum creatinine and may be more appropriate in older patients [40–42]. However, these novel biomarkers may be affected by other non-GFR determinants, such as inflammation, and there is a lack of knowledge regarding their impact among acutely admitted older patients [40, 41]. Therefore, we aim to determine which kidney marker or combination of markers is most accurate for older medical patients, as well as the impact of non-GFR determinants on this accuracy.

#### Malnutrition and nutritional intervention

Malnutrition can lead to decreased physical function and quality of life, rehospitalization, and death [43–45]. Malnutrition among older adults often has a multifactorial etiology [46] including dysphagia [47, 48], poor appetite [49–51], dry mouth [52], problems in the oral cavity [48, 50], polypharmacy [49, 53], hospitalization [50], decreased cognitive capacity, and decreased ability to perform activities of daily living such as cooking, grocery shopping, and eating [48]. Medications can also contribute to the development of malnutrition, as they can induce dry mouth [54], nausea [55], constipation [56], diarrhea [56], and anorexia [57].

The European Society for Clinical Nutrition and Metabolism (ESPEN) recommends that nutritional interventions in older persons should be individualized, multimodal, multidisciplinary, and comprehensive to improve the quality of life. They also recommend that potential causes of malnutrition are systematically identified and eliminated if possible [58]. To our knowledge, however, there is no evidence regarding the effect of a multimodal and transitional nutritional intervention in acutely admitted older medical patients. Therefore, we aim to test the effect of an individualized multimodal and transitional nutritional intervention (MULTI-NUT-MED intervention) among acutely admitted older medical patients using a randomized controlled trial.

### Aims

The study involving acutely admitted older medical patients has three primary aims (1) to determine whether a medication review intervention is superior to standard care in improving medication appropriateness from admission to 8 weeks after discharge, (2) to determine the accuracy of eGFR equations based on various biomarkers compared to mGFR at a single-time point, and (3) to determine whether an individualized multimodal and transitional nutritional intervention is superior to standard care in improving the quality of life from admission and 16 weeks after discharge.

The study also has the following secondary aims which are related to the effect of the intervention: (1) to measure differences in polypharmacy, PIM use, and assessment of underutilization between the MED-intervention and standard care from admission to 8 weeks after discharge and (2) to measure of the differences in body weight, protein- and energy intake, mobility, cognition, frailty, the intestinal microbiome, and health care costs between the MULTI-NUT-MED intervention and standard care from admission to 8 and 16 weeks after discharge and 1 year after discharge (only health care costs).

Secondary aims, which are based on baseline data or data from the control group, include assessment of (1) how information from a broad pharmacogenetic test can potentially improve medication prescribing appropriateness; (2) how polypharmacy, PIMs, nutritional status, frailty, and inflammation modify the effect of the MED-intervention on prescribing appropriateness; (3) how non-GFR determinants affects eGFR and how the choice of eGFR equation affects medication prescribing; (4) how the choice of malnutrition classification criteria affects the prevalence of malnutrition; and (5) how different definitions of frailty affect the distribution of patients classified as frail or sub-frail as well as the responsiveness of these methods.

## Methods: participants, interventions, and outcomes

### Overview and trial design

The OptiNAM trial is a single-center block randomized, controlled, observer-blinded, superiority, and explorative trial with two parallel groups. The trial starts upon admission to the ED and includes follow-up visits at 8 and 16 weeks after discharge and a telephone interview at 1 year after discharge in participants with MNA-SF≤11 to collect EuroQol-5D-5L. Figures 1 and 2 and Table 1 provide schematic overviews of the trial design. The trial was initiated on October 15, 2018, and adheres to the Standard Protocol Items: Recommendations for Interventional Trials (SPIRIT) Statement [59]. Trial registration data (Table 1s) and a SPIRIT checklist are provided in the Supplementary material.

**Fig. 1 Fig1:**
[figure not shown]
Overview of the trial design. Mini Nutritional Assessment-Short Form (MNA-SF), Multidisciplinary (MULTI), Nutritional (NUT), and Medication (MED)

**Fig. 2 Fig2:**
[figure not shown]
Schematic overview of the MULTI-NUT-MED and MED intervention elements and their timeframe. X indicates the timepoint of the intervention element. *These interventions are provided on an individually assessed need. Thus, only the possible timespan of the intervention is indicated. Abbreviations: Multidisciplinary (MULTI), Nutrition (NUT), Medication (MED), and Activities of Daily Living (ADL)

**Table 1 Tab1:** A schematic overview of the study design. Definition of timepoints: t_1_: Within 36 h after admission the ED, t_a_: Immediately after data collection upon enrollment has ended, t_GFR_: During hospitalization or up to 2 weeks after discharge, t_2_: 8 weeks after discharge, t_3_: 16 weeks after discharge, t_1y_: 1 year after discharge. Abbreviations: *GFR* glomerular filtration rate, *MULTI* multidisciplinary, *NUT* nutritional, *MED* medication

Timepoint	Enrollment	Allocation	Post allocation			Close-out
	t_1_	t_a_	t_GFR_	t_2_	t_3_	T_1y_
**Enrolment**						
Eligibility screening	x					
Informed consent	x					
Allocation		x				
Nutritional screening	x					
**Interventions**						
MULTI-NUT-MED intervention		x			x	
MED intervention		x				
**Data collection**						
*Descriptive variables*	x					
**Primary outcomes**						
*Health related quality of life*	x			x	x	x
*Medication appropriateness*	x			x	x	x
*Kidney Function*			x			
**Confirmative outcomes**						
*Underutilization of medication*	x			x	x	
*Energy and protein intake*	During admission			x	x	
*Mobility*	x			x	x	
*Activities of daily living*	x			x	x	
*Well-being*	x			x	x	
*Frailty*	x			x	x	
*Anthropometry*	x			x	x	
*Blood pressure and heart rate*	x			x	x	
*Mortality*					x	x
*Cognition*	x			x	x	
*Depression*	x			x	x	
*Blood samples*	x		x	x	x	
*Health economy*	x				x	x
**Explorative outcomes**						
*Gene variations*	x					
*Body composition*	x		x	x	x	
*Nutritional status*	x			x	x	
*Intestinal microbiota*	x			x	x	

### Setting

The tax-funded Danish health care system is based on the principles of free and equal access to health care for all citizens. In Denmark, there are approximately 1 million acute hospital admissions each year, of which 46% are older persons [1]. This trial is conducted at Copenhagen University Hospital, Hvidovre, Denmark, which covers 10 municipalities with approximately 550,000 citizens and has about 14,000 medical admissions each year of which 85% are acute admissions [36]. The ED has a 29-bed-medical-ward handling acute medical admissions, and a separate emergency room (ER) handling minor injuries and traumas. Patients are referred to the ED by a general practitioner (GP), medical helpline, or emergency phone call. From the ED, a patient can either be discharged or transferred to a specialized medical ward. The hospital does not have a geriatric ward, but the ED is permanently staffed by geriatricians and clinical pharmacists. Dieticians, occupational therapists and physiotherapists are available for consult. Dentists are not part of the normal hospital staff.

### Eligibility criteria, recruitment, and consent

Patients are eligible for inclusion if they are ≥65 years of age, acutely admitted to the ED, community-dwelling, and residing in one of the following municipalities: Hvidovre, Copenhagen (Districts of West and South Western Copenhagen), or Brøndby. Exclusion criteria are inability to understand Danish, inability to cooperate physically (e.g., hearing or speech impairment), or cognitively (e.g., dementia or unconsciousness), isolation room stay, not Caucasian, and admission due to suicide attempt or terminal illness.

Participants are recruited up to 36 h after admission. Each morning (Monday through Thursday), patients are assessed for eligibility from a randomized computer-generated list of all patients in the ED. Eligible patients are informed about the trial both verbally and in writing by a team of seven researchers and are given the possibility of a reflection period of 24 h to consent to participation. Participants are given the option to consent separately to GFR measurement and pharmacogenetic test. After obtaining written informed consent, each participant is randomized to either the intervention group or standard care, and baseline data are collected. After baseline data are collected, each participant is informed about the result of the randomization by staff performing the intervention.

The following strategies are implemented to minimize the effect of staff shortages on patients recruitment: (1) on days with insufficient hospital staff available to perform the MULTI-NUT-MED intervention, only patients with a Mini Nutritional Assessment Short-Form (MNA-SF) [60] score >11 are recruited (to the MED intervention only); (2) on days with insufficient community-based staff available to perform future nutritional intervention (e.g., due to vacation or long term illness), patients from these municipalities are not assessed for eligibility; (3) if more than 35% of the first 50 included patients (*n* = 50) have an MNA-SF score >11, then the project leaders can decide to exclusively recruit patients with an MNA-SF score ≤11 2 days of each week in order to achieve a sufficient number of participants with an MNA-score ≤11 (see the “Sample size” section). The expected recruitment rate is two participants per week for 100 weeks.

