GLIM criteria will be validated against in-depth nutritional assessments performed independently by two blinded and trained nutritional experts (semi-gold standard). The nutritional assessment will include factors related to nutritional status, e.g., dietary intake, factors impeding nutritional intake, appetite, and disease history including LOS and readmissions, body composition, weight history, biochemistry, and physical and psychological wellbeing. The prevalence of malnutrition will be evaluated with descriptive analyses based on specific combinations of phenotypic and etiologic indicators in the GLIM criteria. Finally, statistical agreement analysis between the three malnutrition classifications (MNA-SF, ESPEN, and GLIM) will be evaluated by agreement analysis at admission and up to 16 weeks after discharge. Based on in-depth nutritional assessments, participants only meeting one or two malnutrition classifications will be compared to participants meeting all three malnutrition classifications.

The association between non-GFR determinants and differences between mGFR and eGFR will be evaluated by linear regression analysis. Overall agreement between chronic kidney disease classification based on mGFR and eGFR will be evaluated by Kappa statistics. Results of pharmacogenetic testing including frequency of gene variations and medication interventions based on these variations will be evaluated by descriptive statistics.

Prevalence of frailty will be calculated at baseline and follow-up using three different screening tools (FRAIL, Fried’s frailty phenotype, and FI-OutRef). The effect of the intervention on change in frailty between the baseline and follow-up will be evaluated by mixed models with frailty as the dependent variable and a random effect on participant number, to account for multiple measurements from the same participant. The effect will be measured as an interaction of group and time. Depending on the goodness of fit it may be necessary to categorize frailty. Overall agreement between frailty classification based on the different screening tools will be evaluated by Kappa statistics and mixed models. If the intervention is determined to have a significant effect on frailty, then the agreement between frailty classifications will only be performed using baseline data.

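### Recruitment depends on MNA-SF, contrary to the Sample size section, so pooled malnutrition and frailty prevalences and agreement statistics partly reflect the recruitment rules

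*Protocol article*

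**What the plan says.** All references are to the protocol article.

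- **Eligibility criteria, recruitment, and consent.** Patients are assessed Monday to Thursday. Two rules depend on MNA-SF, and they work in opposite directions.
  - Staff-shortage rule: "on days with insufficient hospital staff available to perform the MULTI-NUT-MED intervention, only patients with a Mini Nutritional Assessment Short-Form (MNA-SF") "score >11 are recruited (to the MED intervention only").
  - Enrichment rule: "if more than 35% of the first 50 included patients" score above 11, the project leaders "can decide to exclusively recruit patients with an MNA-SF score ≤11 2 days of each week". This rule is conditional and discretionary.
- **Abstract, Methods.** The population is described as "70 patients without malnutrition or risk of malnutrition and 130 patients with or at risk of malnutrition".
- **Sample size.** The total of 185 is derived on the statement that inclusion does not depend on nutritional status and that about 70% will be malnourished or at risk. Approval was obtained for 200.
- **Aims.** One secondary aim is "how the choice of malnutrition classification criteria affects the prevalence of malnutrition". The next asks how different frailty definitions change the distribution of patients classed as frail or sub-frail.
- **Statistical methods, Secondary outcomes.** "The prevalence of malnutrition will be evaluated with descriptive analyses based on specific combinations of phenotypic and etiologic indicators in the GLIM criteria". Agreement between MNA-SF, ESPEN and GLIM, frailty prevalence by three tools, and kappa between the frailty tools are also planned, all on the enrolled participants.

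**The concern.** The recruitment rules and the Sample size statement cannot both be right. The rules select on MNA-SF, and MNA-SF is one of the three malnutrition classifications to be compared.

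The other classifications are tied to it. Table 2 has both GLIM and ESPEN start from a malnutrition screen. MNA-SF scores weight development and mobility, while Fried's phenotype and FRAIL score weight loss and walking. A change in the share scoring 11 or less therefore carries through to the pooled GLIM, ESPEN and frailty prevalences and to kappa, which depends on prevalence.

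What is at stake is the interpretation of the descriptive and agreement aims. A reader of the pooled results could not tell how much of a difference between criteria comes from the criteria and how much from the days on which patients were taken.

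**Working it through.** **1. The plan's own figures.**
- 130/0.70 = 185.7, which agrees with the stated 185 (185 × 0.70 = 129.5).
- The 130 follows from a two-sided t test (difference 0.15, SD 0.27, 80% power): 52 per arm, 104 in all, and 104 × 1.25 = 130.
- The 130:70 split is 130/200 = 65%. At the planning share of 70%, 200 patients would give 140.

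**2. How often enrichment becomes available.** More than 35% of 50 means at least 18 patients scoring above 11. With p the true share scoring 11 or less, the binomial probability of at least 18 is 0.22 at p = 70%, 0.76 at 60%, 0.98 at 50% and above 0.999 at 35%. The Background section gives 35–71% for this share.

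**3. Effect of enrichment on the mix.** With two of four days restricted, the share among later patients is 0.5 + 0.5p if each day yields a fixed number, or 2p/(1 + p) if intake is proportional to eligible patients. Let e be that share, applied from patient 51: sample share = (50p + 150e)/200.

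| True p | e (proportional – fixed yield) | Share of 200 |
|---|---|---|
| 35% | 51.9–67.5% | 48–59% |
| 50% | 66.7–75.0% | 62–69% |
| 60% | 75.0–80.0% | 71–75% |
| 70% | 82.4–85.0% | 79–81% |

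**4. Effect of the staff-shortage rule.** The number of such days is not given. If a fraction f of days takes only patients above 11, the share is (1 − f)p with fixed daily yield, or (1 − f)p/[(1 − f)p + 1 − p] with proportional intake. For p = 70% and f assumed at 5–20%, it falls to 56–69%. The two rules oppose each other, so the net direction cannot be stated.

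**5. Effect on the comparison of criteria.** Assume GLIM is positive in a = 60% of those scoring 11 or less and b = 10% of those above. The document gives neither rate. Then:
- GLIM prevalence g = pa + (1 − p)b = 0.10 + 0.5p
- gap between the MNA-SF share and GLIM prevalence = 0.5p − 0.10
- observed agreement = 0.6p + 0.9(1 − p); chance agreement = pg + (1 − p)(1 − g); kappa = (observed − chance)/(1 − chance)

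| Share ≤11 | GLIM prevalence | Gap (points) | Kappa |
|---|---|---|---|
| 35% | 27.5% | 7.5 | 0.53 |
| 50% | 35.0% | 15.0 | 0.50 |
| 65% | 42.5% | 22.5 | 0.44 |
| 70% | 45.0% | 25.0 | 0.40 |
| 71% | 45.5% | 25.5 | 0.40 |

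The criteria behave identically in every row; only the mix differs. For a true share of 50% moved to 62.5–68.75% by enrichment, the gap goes from 15 to 21–24 points and kappa from 0.50 to 0.45–0.41. For a true 70% lowered to 56–69% by staff shortage, the gap goes from 25 to 18–24 points and kappa from 0.40 to 0.48–0.41.

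If MNA-SF itself served as the GLIM screen, b would be 0. The gap would then be 0.4p, that is 14 points at a share of 35% and 26 at 65%, with kappa 0.66 and 0.51. The dependence on the mix remains.

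**6. Frailty.** A shift of the share from 50% to 65% moves a pooled prevalence by 0.15 × (q1 − q0), where q1 and q0 are the rates at 11 or less and above 11. With assumed rates of 50%/30%, 60%/20% and 70%/10%, a pooled 40% becomes 43%, 46% and 49%.

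**The case against.** The strongest objection is that these aims compare definitions within one set of patients. Every criterion is applied to the same people, GLIM is validated against blinded expert assessment rather than MNA-SF, and nutritional status is listed as explorative in Table 1. This limits the importance of the point, but step 5 shows that the within-sample gap and kappa also change with the mix.

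Weighting of a descriptive analysis may also be left to a statistical analysis plan that is not shown. That is fair, and its absence is not the finding. The finding is the contradiction between two sections and its consequence for the planned pooled results.

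Three stronger readings are tempting and are not supported:

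- **That the share is fixed at 65%.** The Abstract states 130 and 70 flatly, but the Sample size section treats 130 as a power requirement and no quota or cap is given. The split is a target. For the same reason, setting 42.5% GLIM prevalence against 27.5% is not a fair measure of the distortion. At a true share of 35% the enrichment rule brings the sample to 48–59%, so on the same assumed rates GLIM prevalence would be about 34–40%.
- **That the trial will publish these as emergency-department prevalences.** No section says so.
- **That the treatment comparisons are affected.** Both arms come from the same intake, so the rules do not bias them.

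**Conclusion.** The contradiction between the recruitment rules and the Sample size section is certain from the text. Its consequence is confined to the descriptive and agreement aims: pooled malnutrition and frailty prevalences, contrasts between criteria and kappa statistics partly reflect recruitment.

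The size is uncertain. Enrichment, if used, would raise the share scoring 11 or less by about 9–24 percentage points over true shares of 35–71%. The staff-shortage rule lowers it by an amount that depends on an unreported number of days. If the true share is the planned 70% and the sample meets its 65% target, the effect is small: 42.5% against 45.0% GLIM prevalence at the assumed rates. The stratum-specific GLIM and frailty rates, the fraction of shortage days and the daily yield are assumptions. The dependence on the mix holds whenever the stratum rates differ.

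This should be put right. It does not threaten the randomised comparisons.

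**What to change.** 1. Correct the Sample size wording so that it acknowledges the two MNA-SF-dependent recruitment rules.
2. Record for each recruiting day whether a restriction was in force, and which one.
3. Report malnutrition and frailty prevalences, and agreement statistics that do not involve MNA-SF, by MNA-SF stratum (≤11, >11).
4. Where a pooled figure or agreement with MNA-SF is wanted, use only patients from days without an MNA-SF restriction, or weight the strata to the ≤11 share seen on those days.
5. Label unweighted pooled figures as reflecting MNA-SF-dependent recruitment, and do not present the sample's ≤11 share as a prevalence.

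The cost is one field in the recruitment log, some extra descriptive analysis and somewhat wider intervals. No new patients or measurements are needed. The weighted figures would still apply only to the consenting, eligible population: community-dwelling patients from the named municipalities, recruited Monday to Thursday.
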